### Randomisation of schools

The 2010 Index of Multiple Deprivation (IMD) [38] is one of the most commonly used indicators of deprivation and the one used in the NCMP. It combines a number of indicators, chosen to cover a range of economic, social and housing issues, into a single deprivation score for each small area in England. Schools will be stratified into low, medium and high IMD tertiles (based on school postcode) by the study team. These data will be provided to the Newcastle Clinical Trials Unit and a statistician, independent to the study team, will randomly allocate the stratified schools in a block design.

### Measures

Parental assessment of their child’s weight statusquestionnaire item: ‘How would you describe your child’s weight at the moment?’ (underweight, healthy weight, overweight, very overweight) [39].visual analogue scale which consists of a 10 cm line with ends labelled ‘extremely underweight’ and ‘extremely overweight’. Respondents mark the spot on the line indicating how they perceive their child’s weight [40].

#### Parent behaviours

Parent knowledge of the health consequences of childhood overweight, intention to change their child lifestyle behaviours (diet and physical activity) and/or seek advice/support, self-efficacy/perceived control over child’s behaviour, action planning, coping planning [23, 26, 27, 36] will be assessed. After a definition of a ‘healthy diet’ there are questions on intention (1 item; “I intend to support my child to have a healthy diet during the next month”), perceived control over child’s behaviour (1 item: how much control do you have over your child’s diet during the next month?), self-efficacy (1 item; “I believe that I can support my child to have a healthy diet during the next month”), action planning (3 items; for example “During the next month I have a detailed plan on what healthy diet my child will eat”) and coping planning (5 items; for example “During the next month I have a detailed plan on what to do if something interferes with my plans to support my child’s healthy diet”). The same constructs are assessed targeting two other relevant behaviours: supporting their children in being physically active and seeking support for their child’s weight. For these two behaviours similar procedures are used: first presenting a definition of the target behaviour, and then asking parents to answer the theory driven items.

#### Anthropometry

Child’s height and weight at baselineChild’s height and weight at 12 month follow-upParents’ weight status based on self-reported height and weight measures

#### Demographic measures

Child’s sexFamily residential postcode

### Sample size

The required sample size is based on detecting a difference in a dichotomous outcome. There are two intervention groups and a control group; the primary comparisons of interest will be between each of the intervention groups and the control group. To take into account the multiple comparisons, the type 1 error rate is specified as 2.5 %. The unit of randomisation is the school.

We estimate the number of eligible children per school completing the study to be 15. This is based on the assumptions that we will survey 120 children per school (2 classes of 30 in each of the two year groups). Of these children we anticipate that 40 (33 %) will meet the study analysis entry criteria (i.e. be overweight) and that of these 20 (50 %) will agree to participate and that of these we will be able to collect follow up data at 12 months for 15 (75 %).

The study is estimated to have 90 % power to detect a 20 point difference between the control group and each of the intervention groups at one month (that is, 30 % of parents accurately perceiving their overweight child as overweight versus 50 %). Applying Fleiss’s method for a proportion incorporating a continuity correction, we would need a final sample size of 471 overweight children (three groups of 157). With an assumed intra-cluster correlation coefficient of 0.01 and a mean cluster size of 15, the design effect is 1 + 14*0.01 = 1.14 implying that we need a final sample size of at least 537 children and thus we will need a minimum of 36 schools. With 120 children per school this will provide a sampling frame of 4320 children. The target sample size is 2160 parent–child pairs.

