This trial will measure parental perception of their child’s weight status, knowledge of the consequences of a child being overweight and intention to change lifestyle behaviours and/or seek advice. Intention will be assessed by items defined by the Target, Action, Context and Time principle [31]. The study will also measure predictors of behaviour change in parents including: perceived control over child’s behaviour and self-efficacy defined as the parent's confidence in performing a behaviour [32, 33]; action planning [32, 34]; coping planning, a barrier-focused strategy to avoid unwanted responses to situational demands or social pressure [35] and measures of parent-reported behaviours aimed at seeking support and facilitating weight control in their children [36].

The aim of the trial is to test whether, compared to controls, providing the Map Me intervention [37] to parents:increases the proportion of parents accurately assessing their child’s weight status (convergent with the UK90 criteria [21])increases parental knowledge of the consequences of their child being overweightimproves parental intention to take action, perceived control over child’s behaviour and self-efficacy, action planning and coping planningis associated with weight status outcomes in children at 12 month follow up

Additionally, differences in the effects of using the web-based and paper-based formats will be investigated.

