### Statistical analysis

Analysis will be restricted to the parents of the overweight children. For the primary outcome measure (dichotomous variable based on correct/incorrect perception of weight status) the null hypothesis is that there is no difference in the proportion of parents with the correct perception of child body weight status between individuals in the control or intervention groups. This will be tested using a logistic multilevel model to account for clustering at school level using specialist statistical software such as MLwiN [41]. Using a multilevel modelling approach will also allow variation in change in perception to be partitioned in to school, year group and individual levels and will permit the inclusion of characteristics of individuals (IMD) and schools (Free School Meal Index and IMD) and anthropometric measures for both child and parent. Inclusion of such terms may reduce the estimate of the standard deviation for the effect and hence provide a more precise estimate of the effect of the intervention. A continuous variable of perception of the child’s weight based on the VAS is also a primary outcome measure.

The secondary outcome measures include knowledge of the consequences of childhood overweight, intention to change lifestyle behaviours and/or seek advice, perceived control, action planning, coping planning, seeking support behaviours, and the child’s body weight status at 12 month follow-up. Process evaluation will use the same statistical approach to test group differences on any of the psychological secondary outcomes.

Although a formal economic analysis is not part of this trial, the study team will work with health economists and use our existing knowledge of the literature to consider the economic implications of our findings.

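### The fixed 2.5% level for each format-versus-control comparison is valid but needlessly conservative; a Holm step-down within 5% gains power at no cost in families

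*Protocol article*

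**What the plan says.** The Sample size section of the protocol article states that "the primary comparisons of interest will be between each of the intervention groups and the control group". It then sets the level: "To take into account the multiple comparisons, the type 1 error rate is specified as 2.5" per cent. The power statement is "The study is estimated to have 90 % power to detect a 20 point difference between the control group and each of the intervention groups", with the difference given as "30 % of parents accurately perceiving their overweight child as overweight versus 50" per cent. The number per group comes from "Applying Fleiss’s method for a proportion incorporating a continuity correction", followed by a design effect of 1.14.

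The Statistical analysis section gives the null hypothesis for the dichotomous outcome ("the null hypothesis is that there is no difference in the proportion of parents with the correct perception") and a logistic multilevel model. It names no significance level and no multiplicity procedure, so the 2.5% in the Sample size section is the only multiplicity rule in the document. The same section calls the continuous VAS perception measure a primary outcome as well.

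**The concern.** Read at face value, the rule is a plain Bonferroni split: each format is compared with control at 2.5%, whatever the other comparison shows. Holm's procedure rejects everything that this split rejects and sometimes more, under the same family-wise limit. A fixed split therefore gives up power for nothing except simpler matching intervals.

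The trial has a direct interest in both formats. Each is a primary comparison, and the aims in the Background add that "differences in the effects of using the web-based and paper-based formats will be investigated". Suppose one format gave p = 0.01 and the other p = 0.03. Under the fixed split the second would not be declared effective, although a 5% family-wise limit would permit the claim. A reader could then wrongly conclude that one format works and the other does not.

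**Working it through.** **Inputs, all from the Sample size section unless noted.** Control 30%, each format 50%; level 2.5% per comparison; power 90%; intra-cluster correlation 0.01; mean cluster size 15; minimum 36 schools. Allocation is 1:1:1 (Procedure section), so 12 schools per arm sharing one control arm. The article does not state whether the level is one- or two-sided.

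**1. Reproduce the plan's figure.** With two-sided 2.5%, z = 2.2414 for the level and 1.2816 for 90% power. The mean proportion is 0.4.

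- Without correction: n = [2.2414·√(2·0.4·0.6) + 1.2816·√(0.3·0.7 + 0.5·0.5)]² / 0.2² = (1.5529 + 0.8692)² / 0.04 ≈ 146.7.
- With continuity correction: n = (146.7/4)·[1 + √(1 + 4/(146.7·0.2))]² ≈ 156.5, rounded up to 157.
- 3 × 157 = 471; 471 × 1.14 = 536.9, rounded up to 537; 536.9/15 = 35.8, rounded up to 36 schools.

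All printed figures reproduce. One-sided 2.5% and two-sided 5% both give 134 per group with the correction, so the printed 157 implies a two-sided 2.5% test for each comparison.

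**2. Chance of showing both formats at fixed 2.5%.** The two contrasts share the control arm, so their correlation when both formats are at 50% is 0.21/(0.21 + 0.25) = 0.457. With 90% power for each, the bivariate normal probability that both succeed is 83.0%. At least one succeeds with probability 0.90 + 0.90 − 0.83 = 97%.

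**3. Simulation of both rules.** Two million binomial trials were run at 157 per arm (the effective size after the design effect), with pooled-variance z-tests.

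| Both formats 50% vs 30% | Each, fixed 2.5% | Each, Holm | Both, fixed 2.5% | Both, Holm |
|---|---|---|---|---|
| Continuity-corrected | 90.1% | 93.3% | 83.3% | 89.7% |
| Uncorrected | 92.0% | 94.7% | 86.2% | 91.7% |

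Normal theory set to 90% for each comparison gives 83.0% for both at fixed 2.5% and 89.2% under Holm. Simulating the clusters directly (12 schools of 15 per arm, correlation 0.01) gives 83.6% against 89.7% with the correction and 86.3% against 91.7% without it.

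**4. One format weaker (50% and 45%).** Direct check for the weaker format at fixed 2.5%, uncorrected, with effective n = 180/1.14 = 157.9: the null standard error is √(2·0.375·0.625/157.9) = 0.0545 and the alternative standard error is √((0.21 + 0.2475)/157.9) = 0.0538. Then (0.15 − 2.2414·0.0545)/0.0538 ≈ 0.52, which is power of about 70%. In simulation, its power rises under Holm from 65.7% to 74.0% (corrected) or from 69.8% to 77.7% (uncorrected).

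**5. Only one format works.** Power for that format is 90.1% under either rule (corrected tests).

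**6. Error control.** If both null hypotheses are true, any false claim needs the smaller p-value to fall at or below 2.5%, with probability at most 2 × 2.5% = 5%. Holm and the fixed split coincide there; the simulated rate with uncorrected tests is 4.7%. If one null hypothesis is true, rejecting it needs its own p-value at or below 5%. In simulation with the other format at 50%, false claims under Holm were 3.4% (corrected) and 4.7% (uncorrected).

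**The case against.** The strongest objection is that nothing printed is wrong. A reader might infer that the 90% overstates the trial's power, because showing both formats has a probability nearer 83% to 86%. The document does not support that reading. It promises "90 % power to detect a 20 point difference between the control group and each of the intervention groups", which is power per comparison, and that figure is right. Nowhere does it state a joint power or make success depend on both formats. Power for at least one format is about 97% to 98% under either rule.

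A second objection is that the 2.5% appears only in the Sample size section. Sizing at 2.5% is compatible with Holm's first step, and an analysis plan that is not shown could adopt Holm. It is therefore too strong to infer that the trial is bound to leave a second format with p = 0.03 unproven. This point stands, but 2.5% is still the only rule stated, and a better one can be written in its place.

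Third, the Bonferroni split is a valid choice with simple simultaneous 97.5% intervals that match its decisions. This also stands, and it is the one real cost of changing.

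Fourth, the direct comparison of web with paper announced in the aims is a separate question. Holm on the two comparisons with control does not address it.

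**Conclusion.** This is a cheap improvement and not the correction of an error. The sample size and the 90% are correct for each comparison singly at two-sided 2.5%, and the claim that the 90% is misstated does not hold. What holds is that the fixed split is more conservative than a 5% family-wise limit requires.

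If both formats truly reach 50%, Holm lifts the chance of showing both from about 83%–86% to about 90%–92% (89% by normal approximation), and power per comparison by about 3 points. For a weaker format at 45%, the gain is about 8 points. If only one format works, there is essentially no gain.

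These figures assume an intra-cluster correlation of 0.01, equal arms of the planned size, and z-tests adjusted by the design effect in place of the planned logistic multilevel model. They also assume that the dichotomous outcome keeps the full 5%. The error statement covers only its two comparisons with control, and the VAS is outside it.

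**What to change.** Keep the sample size. In the Sample size and Statistical analysis sections, or in the analysis plan before results are seen, prespecify Holm for the two format-versus-control comparisons on the dichotomous primary outcome: test the smaller p-value at two-sided 2.5% and, if it is significant, the other at 5%. If part of the 5% is assigned to the VAS, apply Holm within the share left to the dichotomous outcome and recompute the power figures.

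The power sentence may add that 90% refers to each comparison taken singly at 2.5%. If a joint figure is wanted, give it with its assumptions: about 83% to 86% at fixed 2.5%, and about 90% to 92% under Holm.

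The cost is a sentence of text, with no extra schools, families or data. The drawback is that intervals matching step-down decisions are less simple; 97.5% intervals can still be reported descriptively.

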### Statistical analysis

Analysis will be restricted to the parents of the overweight children. For the primary outcome measure (dichotomous variable based on correct/incorrect perception of weight status) the null hypothesis is that there is no difference in the proportion of parents with the correct perception of child body weight status between individuals in the control or intervention groups. This will be tested using a logistic multilevel model to account for clustering at school level using specialist statistical software such as MLwiN [41]. Using a multilevel modelling approach will also allow variation in change in perception to be partitioned in to school, year group and individual levels and will permit the inclusion of characteristics of individuals (IMD) and schools (Free School Meal Index and IMD) and anthropometric measures for both child and parent. Inclusion of such terms may reduce the estimate of the standard deviation for the effect and hence provide a more precise estimate of the effect of the intervention. A continuous variable of perception of the child’s weight based on the VAS is also a primary outcome measure.

The secondary outcome measures include knowledge of the consequences of childhood overweight, intention to change lifestyle behaviours and/or seek advice, perceived control, action planning, coping planning, seeking support behaviours, and the child’s body weight status at 12 month follow-up. Process evaluation will use the same statistical approach to test group differences on any of the psychological secondary outcomes.

Although a formal economic analysis is not part of this trial, the study team will work with health economists and use our existing knowledge of the literature to consider the economic implications of our findings.

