**Design:**

This cluster randomised trial will test the effectiveness of the Map Me intervention. Primary schools will be randomised to: paper-based Map Me; web-based Map Me; no information (control). Parents of reception (4–5 years) and year 6 (10–11 years) children attending the schools will be recruited. The study will work with the National Child Measurement Programme which measures the height and weight of these year groups and provides feedback to parents about their child’s weight status. Before receiving the feedback, parents will complete a questionnaire which includes assessment of their perception of their child’s weight status and knowledge of the health consequences of childhood overweight. The control group will provide pre-intervention data with assessment soon after recruitment; the intervention groups will provide post-intervention data after access to Map Me for one month. The study will subsequently obtain the child height and weight measurements from the National Child Measurement Programme. Families will be followed-up by the study team at 12 months. The primary outcome is any difference in accuracy in parental perception of child weight status between pre-intervention and post-intervention at one month. The secondary outcomes include differences in parent knowledge, intention to change lifestyle behaviours and/or seek advice or support, perceived control, action planning, coping planning, and child weight status at 12 month follow-up.

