**Discussion:**

The Map Me tool has potential to make a positive impact on children’s health at a population level by introducing it into current intervention programmes to improve accuracy of parental perception of child’s weight status. This trial will inform the action of researchers, educators, health professionals and policy makers.

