### Procedure

Within schools, all the parents of 4–5 and 10–11 year old children will be sent an invitation to join the study. Recruited parents will be those who return a signed consent form. Every school that has at least one consented child will be randomised to Intervention A, Intervention B or control using a 1:1:1 ratio, as described in the ‘randomisation of schools’ section.

Parents in the control group will provide the baseline data for the trial. They will not receive either intervention during the study period. They will be posted the study questionnaire soon after the study team receive their consent forms; the questionnaire consists of the outcome and explanatory measures. Parents in the intervention groups will receive the intervention by post. Those randomly assigned to the web-based version will additionally receive a follow-up email with website link, if an email address was obtained. The intervention period lasts four weeks and after this period has elapsed all parents in the intervention groups will be posted the study questionnaire. Parents will be asked to complete and return the questionnaire to the study office in the provided postage-paid envelope. In the majority of cases, the study team will obtain the child height and weight measurements from the NCMP. All parents and children will be followed up at 12 months after the first day of the intervention; parents will be sent the study questionnaire to complete and return to the study office, and the children will be measured for height and weight by the study team, usually at school.

A favourable ethical opinion was obtained from National Research Ethics Service, Committee North East - Newcastle and North Tyneside 2: reference 12/NE/0409.

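### Every analysis is limited to parents of overweight children, while the stated aim and primary outcome are accuracy of weight perception without that limit, so over-labelling of other children goes unexamined

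*Protocol article*

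**What the plan says.** The Statistical analysis section opens with "Analysis will be restricted to the parents of the overweight children". The null hypothesis that follows, that "there is no difference in the proportion of parents with the correct perception of child body weight status" between arms, is therefore tested only within that group. The Sample size section is consistent with this. It treats being overweight as the criterion for entering the analysis and bases power on 30% versus 50% of parents of overweight children recognising the overweight.

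Other sections are worded more widely:

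- **Aim (end of Background):** whether Map Me "increases the proportion of parents accurately assessing their child’s weight status", judged against the UK90 criteria.
- **Primary outcome (abstract, Design):** "The primary outcome is any difference in accuracy in parental perception of child weight status" between pre-intervention and post-intervention at one month.
- **Who takes part (Procedure):** "all the parents of 4–5 and 10–11 year old children will be sent an invitation to join the study". Consenting parents in intervention schools receive Map Me, and all consenting parents receive the questionnaire, whatever the child's weight.
- **What is measured (Measures):** a perception item with four categories from underweight to very overweight, and a visual analogue scale.
- **Intended use (abstract, Discussion):** population-level benefit "by introducing it into current intervention programmes to improve accuracy of parental perception" of the child's weight status.

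No section describes an analysis of parents whose child is not overweight.

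**The concern.** Among overweight children, the proportion of parents who are correct is the sensitivity of parental labelling. It says nothing about whether parents of healthy-weight or underweight children still label them correctly. An intervention can raise sensitivity by helping parents discriminate better, or by moving answers upward in general. The planned comparison cannot tell these apart. The visual analogue scale, also named as a primary outcome, falls under the same restriction and offers no check.

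At stake is the conclusion the trial may draw. A positive result would support a statement about recognition of overweight. It would not support one about accuracy of parental perception, which is how the aim, the abstract's primary outcome and the proposed use are worded. The restriction is written into the protocol, so it is not a detail left open for an analysis plan.

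**Working it through.** **1. Inputs, all from the Sample size section unless marked.** Overweight share 40/120 = 33%; participation 50%; retention 75% at 12 months; 30% versus 50% correct; type 1 error 2.5%; power 90%; ICC 0.01; cluster size 15; 36 schools; 120 children per school; target 2160 pairs. Allocation is 1:1:1 (Procedure).

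**2. The plan's own figure reproduces.** Fleiss's formula with continuity correction, two-sided 2.5%, 90% power, 30% versus 50%, gives 157 per group. Then 3 × 157 = 471; design effect 1 + 14 × 0.01 = 1.14; 471 × 1.14 = 536.9, rounded up to 537; 537/15 = 35.8, rounded up to 36 schools; 36 × 120 = 4320; 4320 × 0.5 = 2160. The sample size is not in dispute.

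**3. Break-even for overall accuracy.** With overweight share p, a gain g among overweight children and a loss of correct labelling L among the rest, the change in overall accuracy is p × g − (1 − p) × L.

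- Gain alone: 1/3 × 20 = 6.7 points.
- Break-even: L = p × g/(1 − p) = (1/3 × 20)/(2/3) = 10 points.

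This does not depend on the control-arm level of accuracy. It does depend on p:

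| Overweight share | Loss among the rest that cancels a 20-point gain |
|---|---|
| 20% | 5.0 points |
| 25% | 6.7 points |
| 33% | 10.0 points |
| 40% | 13.3 points |

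**4. An equal shift in both groups.** Suppose 20 points more of all parents call their child overweight, and in the non-overweight group this replaces correct answers. The change is 1/3 × 20 − 2/3 × 20 = −6.7 points. For example, if control accuracy in non-overweight children were 98% (assumed), overall accuracy would go from 1/3 × 30 + 2/3 × 98 = 75.3% to 1/3 × 50 + 2/3 × 78 = 68.7%. The planned analysis would show the full 30% to 50% effect.

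**5. Data available for a check.** Non-overweight pairs: 2160 × 2/3 = 1440. At 75% retention (stated for 12 months and used here also for one month): 1080, or 360 per arm, which is 1080/36 = 30 per school. The design effect is 1 + 29 × ICC. Power at two-sided 2.5%, without continuity correction and with levels of correct labelling assumed:

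| Fall in correct labelling | ICC 0.01 (effective n per arm 360/1.29 = 279) | ICC 0.05, assumed (360/2.45 = 147) |
|---|---|---|
| 95% to 85% | 96% | 73% |
| 90% to 80% | 86% | 56% |
| 95% to 90% | 50% | 27% |

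The article assumes 0.01 for perception among overweight children. It gives no ICC for the rest.

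**The case against.** The restriction looks deliberate. The Background gives the problem as parents of overweight children not describing them as overweight. The main Discussion describes the trial as a test of whether Map Me improves perception of overweight, and the Sample size section is built on that group. This stands: it justifies the overweight-only primary comparison. It does not reconcile that comparison, as the sole analysis, with an aim and outcome worded without the limit.

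Four stronger readings are tempting and are not supported:

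- **That any general upward shift would count as success.** The item has four categories and the article does not settle whether correct means the exact category. If it does, moving an overweight child to very overweight is an error. The point holds for a moderate shift.
- **That over-labelling is likely, or the main harm of roll-out.** Nothing in the article says so. The scales contain three healthy-weight levels, the paper version labels each image, and the web version moves the chosen image to the correct one, so feedback is calibrated in both directions. Over-labelling is a possibility to be checked.
- **That the trial could not detect it.** The questionnaire goes to every pair, and child measurements come from the national programme in most cases. What is missing is a planned analysis.
- **That knowledge and the psychological outcomes must also be analysed in all parents.** Pooling would change the target population and might dilute effects that depend on first recognising overweight. That is a choice for the investigators, not an error.

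**Conclusion.** The point holds in limited form. The primary comparison is reasonable for the problem stated, but on its own it cannot support a conclusion about accuracy of parental perception in general. Under the article's own 33% and 20 points, the whole overall gain is 6.7 points and a 10-point loss elsewhere removes it. Under an equal 20-point shift, overall accuracy would be 6.7 points worse while the trial reported its full target effect.

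These figures show what the plan would leave unseen and do not predict what will happen. The break-even rests on the overweight share among participants matching the planning figure. The power figures rest also on assumed levels of correct labelling and an ICC that the article does not give for this group. A 10-point loss would probably be found, but a 5-point loss could well be missed even at an ICC of 0.01. The change is recommended; it does not call the primary test or the sample size into question.

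**What to change.** Keep the overweight-only comparison as primary and lift the blanket restriction for one pre-specified secondary analysis in the same multilevel model, with two parts reported beside the primary result:

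1. the proportion of parents of non-overweight children who label the child overweight or very overweight, by arm;
2. the proportion of all participants whose label is correct against the UK90 criteria, by arm.

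State whether correct means the exact category, since both analyses depend on it. Report confidence intervals rather than relying on a test, because precision for small losses is limited and depends on the ICC.

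The alternative is to narrow the first aim, the primary outcome in the abstract and the conclusion to recognition of overweight by parents of overweight children. This settles the mismatch of wording but leaves over-labelling unexamined.

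The first option costs a few extra models on data already due to be collected. Recruitment, questionnaires and power for the primary comparison are unchanged. The second costs only wording.

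### Year group is named only as a variance level; stating it also as a fixed covariate would protect the standard error of the intervention effect if reception and year 6 differ widely

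*Protocol article*

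**What the plan says.** The primary outcome is whether the parent of an overweight child perceives the child's weight status correctly. On the primary test, the Statistical analysis section says: "This will be tested using a logistic multilevel model to account for clustering at school level". It adds that the approach will also allow "variation in change in perception to be partitioned in to school, year group and individual levels", and that it "will permit the inclusion of characteristics of individuals (IMD) and schools (Free School Meal Index and IMD) and anthropometric measures for both child and parent". The reason given for the extra terms is that they may make the estimated intervention effect more precise.

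Year group therefore appears as a level and not in the list of covariates. The section does not say whether it is nested in school or crossed with it; the order of the levels suggests nesting. Nor does it say that a fixed year-group term is excluded.

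Under Sample size, each school is assumed to supply "2 classes of 30 in each of the two year groups", and "The unit of randomisation is the school". The calculation claims "90 % power to detect a 20 point difference between the control group and each of the intervention groups at one month" and allows for clustering by school only.

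**The concern.** Reception and year 6 are not a sample from a population of year groups. They are the two categories of interest and both recur in every school. Because whole schools are randomised, each arm contains both years, so an age difference in accuracy should cancel from the comparison between arms.

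A model with a random year-within-school intercept and no fixed year term does not credit that balance. It treats a consistent gap as if each school-by-year group had drawn its own independent deviation. That variance then enters the standard error of the intervention effect, although the estimate itself does not vary more. Confidence intervals would be too wide and power would be lost for a reason unrelated to sample size. That runs against the section's own aim of greater precision.

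**Working it through.** **Inputs from the document.** 30% v 50% correct perception; 90% power; "the type 1 error rate is specified as 2.5" per cent; 157 per group; ICC 0.01; mean cluster size 15; 36 schools allocated 1:1:1, so 12 per arm. Sidedness is not stated.

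**The plan's own figure.** With two-sided alpha 0.025, z = 2.2414 and 1.2816:

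- n′ = [2.2414·√(2·0.4·0.6) + 1.2816·√(0.3·0.7 + 0.5·0.5)]² / 0.2² = 2.4221² / 0.04 = 146.7
- With continuity correction: (146.7/4)·[1 + √(1 + 4/(146.7·0.2))]² = 156.5, so 157
- 3 × 157 = 471; 471 × 1.14 = 536.9, so 537; 537/15 = 35.8, so 36 schools

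The sample size reproduces exactly as two-sided. A one-sided test would give 134 per group.

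**Size of the effect by hand.** Let d be the log-odds gap between the year groups. It is an assumption. In a nested model without a fixed year term, each school-by-year unit deviates by ±d/2, which the model reads as variance (d/2)². Each arm has 12 × 2 = 24 such units (72 in all), so the variance added to the arm contrast is about 2·(d/2)²/24. Adding this to the squared standard error from the fixed-year model below:

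- d = 1.0: 0.242² + 2·0.25/24 = 0.0586 + 0.0208 = 0.0794, SE about 0.28
- d = 1.5: 0.249² + 2·0.5625/24 = 0.0620 + 0.0469 = 0.1089, SE about 0.33

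**Simulation.** 400 trials per scenario: 12 schools per arm, 15 children per school split 7/8 by year, ICC 0.01, marginal rates 30% v 50%, two-sided 2.5%, logistic mixed models fitted by Gauss-Hermite maximum likelihood. Gaps of 0, 0.5, 1.0 and 1.5 give control rates of about 30/30, 25/35, 20/40 and 15/45%. Each SE pair is mean model SE / empirical SD of the estimate.

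| Gap d (points) | Nested random year only: power; SE pair | Fixed year + random school: power; SE pair | Nested random + fixed year: power |
|---|---|---|---|
| 0 (0) | 0.938; 0.236/0.224 | 0.943; 0.233/0.224 | 0.938 |
| 0.5 (about 10) | 0.902; 0.242/0.245 | 0.912; 0.236/0.246 | 0.905 |
| 1.0 (about 20) | 0.873; 0.274/0.246 | 0.943; 0.242/0.248 | 0.943 |
| 1.5 (about 30) | 0.800; 0.332/0.253 | 0.950; 0.249/0.255 | 0.945 |

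The simulated standard errors of 0.274 and 0.332 agree with the hand figures. The empirical SD is almost the same under every model, so the problem lies in the reported standard error: 0.274/0.246 = 1.11 and 0.332/0.253 = 1.31.

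A separate set of 900 trials per scenario, two comparisons each, gave the same pattern:

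- 10-point gap: 92% (nested random) v 94% (fixed year)
- 20-point gap: 90% v 95%; SE 0.271 against SD 0.243, ratio 1.12; type I error 1.5%
- 30-point gap: 81% v 96%; SE 0.335 against SD 0.242, ratio 1.38; type I error 0.4%

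**Other readings of the model (ICC 0.01).**

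- Year group as one crossed random factor with two categories (approximate fit, 200 runs, d = 0.5, 1.0, 1.5): SE 0.233, 0.239, 0.246 against 0.233, 0.240, 0.247 for fixed year in the same runs; power identical at 0.91, 0.95, 0.95.
- School random intercept only, year group ignored: power 0.912, 0.940, 0.938 at the same gaps, so no material loss.

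**Sensitivity at ICC 0.05.** Nested random only v fixed year: 0.835 v 0.855, 0.792 v 0.838, 0.733 v 0.877, losses of about 2, 5 and 14 points. Here the fixed-year standard error is itself somewhat low (0.275 against an SD of 0.302 at d = 1.0), so these differences show direction more than exact size.

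**The case against.** The strongest reply is that the text fixes less than the concern needs. The primary test is described once, as accounting for school clustering; the year-group level comes in a following sentence about what the approach allows and permits. The covariate list is not declared complete, and a level and a fixed term can coexist. A reader might infer that the plan chooses a random year group in place of a fixed one. The document does not say so, and a condensed article may leave the final list of terms to the analysis plan. This stands, and it limits the point to a conditional one. What remains is that the only role the article gives year group is the one that, used alone under nesting, can do harm.

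A reader might also infer that the trouble is a random factor with just two categories. That describes the crossed model, whose variance component would be poorly estimated but which does not inflate the standard error of the intervention effect. The inflation belongs to the nested model, with its 72 school-by-year units.

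Nor does any systematic difference cost power. At a 10-point gap the loss is within or close to the Monte Carlo error of 1–2 points. At 20 points one set of simulations still gives the promised 90%, the other 87%.

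Finally, the covariates mentioned include child anthropometry. If raw height and weight were entered, they would largely separate the two ages and absorb much of a gap; BMI centiles would not. The document does not say which, and the simulations tested neither.

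**Conclusion.** The point holds in conditional form. If year group is a random level nested in school with no fixed year-group term, a large systematic difference between reception and year 6 makes the standard error too large and the test conservative. At ICC 0.01 the loss is about 1–2 points of power for a 10-point gap, 5–7 for a 20-point gap (standard error about 11–12% too large) and 15 for a 30-point gap (about 80% v 95%). With no gap, or with a crossed two-category factor, there is no material loss.

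This rests on an assumed gap, the nested reading, and no other covariate standing in for age. It would be tempting to conclude that the stated 90% power is wrong. The documents do not support that: the calculation reproduces, and erosion depends on a gap they do not give. There is no bias and no excess of false positives from this source; the error is in the cautious direction. It is a free improvement.

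**What to change.** State year group (reception or year 6) as a fixed binary covariate in the primary logistic multilevel model, with school as a random effect. A year-within-school random intercept may be kept in addition to the fixed term, but not in place of it: with both, power was 0.943 and 0.945 at the 20- and 30-point gaps, almost the same as with the fixed term and school alone. There is no need to drop that level.

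The cost is one line of model specification. Year group is already known for every child, no extra data are needed, and nothing appreciable is lost if the year groups do not differ (power 0.943 with fixed year and random school, 0.938 with the nested level alone or with both). The change should be settled before outcome data by arm are examined.
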